### Ethical considerations

➣ All aspects of human subject research ethics will be fully observed in this research. All exemptions and approvals will be checked and observed by the researchers. Also, this research has a code of ethics from Shahid Beheshti University of Medical Sciences. IR.SBMU.PHNS.REC.1400.073(.➣ Informed consent will be obtained from all study participants at all stages. In addition, informed consent will be obtained from adolescents, their parents, or legal guardians to participate in the study. Also, in the initial informed consent received from the participants, it will be mentioned that the possibility of secondary analysis is possible without additional consent. Participants will also be assured of their voluntary participation in the research and their freedom to withdraw from the study at any stage of the research.➣ The data obtained from the study remains confidential and anonymous in the study. Participants will also be assured that the information will remain confidential. In the reports and presentation of the results, no connection between the data and the profile of the participant will be given, so that the participants will not be identified.➣ This study will not involve any therapeutic or invasive procedures. During the implementation of the research, there will be no threat of physical, financial, or social harm to people.

## Results

Our findings are scheduled for a full analysis, with expectations that analyses will be completed by September 2023. We intend to publish results in peer-reviewed journals.

It is expected based on the objectives of the study:

The self-care mobile application should be designed in a scientific and user-oriented way and should be usable in the target group. We also expect users to be satisfied with the application, consider it useful, and evaluate it as easy to use.

Also, we expect that at the end of the research, a questionnaire measuring the self-care performance of adolescents will be designed, and it will have appropriate validity and reliability, and it can be used in other studies and populations.

Based on the objectives of the third stage of the study, we expect that the educational intervention in the intervention group, through the use of the designed mobile application, will improve self-care behaviors in terms of physical activity, nutrition, personal hygiene, risky behaviors, and safety and events.

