### General goals

This study has three general goals:Design and evaluation of a mobile application for adolescent self-care.Designing and evaluating psychometric properties of “Questionnaire for Measuring Adolescent Self-Care Performance.”Determining the effectiveness of self-care interventions based on mobile application among adolescents.

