#### The third stage

The next stage of the sampling method is cluster random. From 337 government schools and 93 non-government schools, based on the list of urban schools received from the Department of Education, two boys’ schools and two girls’ schools are randomly selected. Then, one boy’s school and one girl’s school will be randomly assigned as the intervention group and one boy’s school and one girl’s school will be in the control group, and the sampling of students of different grades of the selected schools will be simple cluster or random. Sampling of students from different grades from selected schools will be simple in cluster or random. The sample size was calculated according to the formula of 43 people in each group. Taking into account 15% attrition, the sample size was determined to be 50 people in each group. The study will be conducted on 100 students of Amol City. Of these, 50 people will be assigned to the intervention group and 50 people will be assigned to the control group. From each school, 25 samples were selected (Fig. 2).

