**Fig. 2 Fig2:**
[figure not shown]
The study sampling stages

$$n= \frac{{2\left(Z1-\frac{\alpha }{2}+ Z1-\beta \right)}^{2}}{{\left(\frac{\Delta }{S}\right)}^{2}}$$

The schools selected for the intervention and control groups will be far apart in order to prevent contamination bias. The effects of confounding variables such as economic status and social class will be controlled in the clusters in the data analysis with the covariance test. All samples, education office, school managers, and user panel managers will be blinded.

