#### Stage III

The third stage is an interventional method of experimental study. This research will be conducted through a pre-test-post-test design with a control group. All the students studying in schools constitute the research community. The researcher first introduces the adolescents to the full explanation of the research and its goals. Then informed written consent will be obtained from the volunteers. None of the participants will be subject to any other research intervention. Schools will be randomly assigned to one of the two intervention (group 1) and control (group 2) groups. The full content of the program will be visible only to the participants in the intervention group. Participants in the control group will be able to download the app after the end of the intervention to use the educational benefits of the app. A self-care application can be used online and offline designed for smartphones running the Android operating system. To run this test, eligible students are asked to install the self-care app on their smartphone and see the necessary instructions on how to work with the program in the form of a short guide on the main page of the application. Initially, the participants are asked to complete the self-care questionnaire in the form of a pre-test. Then, the educational content designed for the application is provided for individuals based on national and international guidelines and protocols of (WHO, CDC, FDA, ADF, Ministry of Health and Medicine, Health Education and Health Promotion Office). This program will be available to people for 3 months and after installing the application on their smartphone and entering the information requested from the users, educational content and reminder messages will be sent according to their conditions. In the reminders section, the user registers his health behavior based on the day, time, and number of times he wants, and a reminder is sent to him. But if the user’s self-care status after answering the self-care questions in each of the 5 dimensions of self-care is assessed as weak or average, motivational health messages are sent to the user daily in the form of notifications, so that the user is encouraged to perform self-care behaviors. The use of the application by the participants is reviewed in the management panel and health messages and incentives are provided for the use of this program. To provide support, the researcher’s phone number is given to the subjects to make a call in case of problems. Three months after the intervention, when no new content is sent to the student, the participants in both groups are requested to complete the self-care questionnaire in the form of a post-test. After the end of the data collection process, the individuals in the control group can install a mobile Application and the necessary training will be given to them after the end of the study. In the present study, content, information, and experiences reach the end users or audience with the specific purpose of self-care through mobile applications in the form of text, audio, or other art forms. Users find and use health-related self-care information through content. The graphic design of the application is based on the opinion of the research team professional designers and application development experts. The production of the content is based on the points extracted from the interviews, national and international guidelines, and protocols of (WHO, CDC, FDA, Ministry of Health and Medicine, Health Education and Health Promotion Office), for example, Australian dietary guidelines, Canberra: NHMRC [20], WHO guidelines on physical activity and sedentary behavior for children and adolescents aged 5–17 years: summary of the evidence [21], and physical activity guidelines [22].

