### Methods of analysis

In the first stage, after the interviews are completed, all the interviews will be transcribed verbatim and entered into NVIVO 12 (Qualitative Analysis Software) for data management. Demographic data will be encoded and analyzed using Microsoft Excel software to determine central indicators and values in a sampling distribution. The data will be analyzed to provide a simple descriptive summary of participants’ opinions presented in everyday language. Specifically, the data will be coded for all the participants and classified to reflect the main themes. In the second stage, we employ factor analysis which is a statistical method that determines the number and nature of variables that a test measures. Following this method, variables with homogeneous correlations are categorized in the form of new variables called factors. The purpose of exploratory factor analysis is to discover the dimensions and common applications including instrument dimensions, standardization of questionnaires or tests, dimensionality, and evaluation of consistency and differentiation in the discussion of construct validity [23]. In the third stage, descriptive statistics (frequency, frequency percentage, mean, and standard deviation) will be used to analyze the data. The Kolmogorov–Smirnov test will also be used to check the normality of quantitative variables. Between-group and within-group comparisons about quantitative variables, independent *t*-test and paired *t*-test, and analysis of variance will be calculated. The chi-square test and Fisher’s exact test in SPSS 16 software will be utilized to test the homogeneity of qualitative variables between the two groups.

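### Stage 3 names no outcome score and no comparison that decides effectiveness, although its sample size formula is for a single comparison

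*Protocol article*

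**What the plan says.** The stage 3 goal in the General goals section is broad: "Determining the effectiveness of self-care interventions based on mobile application among adolescents". Under Study process, Stage III, one instrument is given before and after the intervention, and at the end "the participants in both groups are requested to complete the self-care questionnaire in the form of a post-test". The same section refers to "self-care questions in each of the 5 dimensions of self-care", but there the dimensions decide who receives motivational messages; they are not called trial outcomes. The Results section, writing of what is expected from the stage 3 objectives, says the intervention "will improve self-care behaviors in terms of physical activity, nutrition, personal hygiene, risky behaviors, and safety and events".

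Methods of analysis covers "Between-group and within-group comparisons about quantitative variables" with independent t-tests, paired t-tests and analysis of variance. None of these is called the main analysis. The text with Figure 2 adds that confounders such as economic status will be "controlled in the clusters in the data analysis with the covariance test".

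On size, the third-stage sampling section says "The sample size was calculated according to the formula of 43 people in each group", raised to 50 for 15% attrition. The formula shown has one standardised difference (Delta/S), one two-sided alpha and one power. No values are given for these, and the score to which Delta/S belongs is not named. Four schools are randomised, two per arm, with 25 students from each.

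**The concern.** An effectiveness trial needs one result that answers its question, and the sample size has to be the size for that result. Here the reader cannot tell whether the answer lies in a total questionnaire score, in one of five domain scores, or in all five. Nor can the reader tell whether it comes from a comparison between arms or from change within the intervention arm. This belongs in the protocol and cannot simply be left to an analysis plan, because 43 per group has no meaning until the outcome behind Delta/S is named.

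Two things are at stake. First, if the choice is made after stage 3 data are seen, a favourable domain can be singled out and the error rate of the effectiveness claim rises. Second, the paired tests have the same standing as the between-arm tests. A pre-to-post change over three months in adolescents can come from the passage of time, maturation or answering the same questionnaire twice. A significant paired test in the app group is not evidence that the app worked.

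**Working it through.** **The plan's own figure.** 43 × 1.15 = 49.45, rounded up to 50; 43 / 0.85 = 50.6, rounded up to 51. The stated 50 is reproduced to within one. The 43 cannot be checked because its inputs are not given. At an assumed two-sided 5%, n = 2(z₁₋α/₂ + z₁₋β)² / (Delta/S)² gives 43 with Delta/S of about 0.604 at 80% power or 0.70 at 90% power. The 43 is plausible for one comparison.

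**Inputs for the error rate.** Five domains (Results section). Assumed, because the article gives none of them: alpha of two-sided 5%, each domain tested separately, equal correlation between domain statistics from 0 to 0.9, and no clustering.

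**Reading A: any one domain suffices.** With independent domains, the chance of at least one false positive in either direction is 1 − 0.95⁵ = 22.6%. In the direction of benefit it is 1 − 0.975⁵ = 11.9%. With correlated domains (simulation, 2 million draws):

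| Correlation | Either direction | Benefit direction |
|---|---|---|
| 0 | 22.6% | 11.9% |
| 0.5 | 18.3% | 9.1% |
| 0.7 | 14.9% | 7.4% |
| 0.8 | 12.8% | 6.4% |
| 0.9 | 10.2% | 5.1% |

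The values for a single test are 5% and 2.5%.

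These figures cover between-arm tests only. Adding five paired tests in the intervention arm, and assuming no time trend, gives about 35% (correlation 0) or 29% (0.5) in either direction, and 19% or 14% in the benefit direction. With a real time trend the paired tests would reject more often still, for reasons unrelated to the app.

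**Reading B: all five domains must improve.** Error is not inflated, but power falls. If 43 per group gave 80% power for each domain (assumed), power for all five is 0.8⁵ = 33% if independent, about 51% at correlation 0.5 and 59% at 0.7. If 43 was set for 90% power, the figures are 0.9⁵ = 59%, 71% and 76%. In both cases power is below what the formula was set to give.

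**Reading C: one overall score.** This is the only reading that matches a one-comparison formula, and the article does not state it.

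**Would one named outcome restore 5%?** Not by itself. A student-level t-test on one outcome, with two randomised schools per arm and 25 students each, was simulated under no effect. The false-positive rate was about 8%, 11%, 19% and 30% at assumed intraclass correlations of 0.01, 0.02, 0.05 and 0.10.

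**The case against.** The strongest reply is that the article never says the domains will be tested separately, and never says one significant domain would count as success. The five areas are listed in a statement of expectation and joined by "and". They can be read as describing the content of one construct measured by one questionnaire. A multiplicity procedure may also sit in an analysis plan that is not shown, and a condensed article need not contain one.

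Most of this stands. A reader might infer that the plan carries a 15–23% chance of falsely claiming benefit. The article does not support that. The range counts errors in both directions, needs an any-domain rule and a 5% alpha that are not stated, and stops at a correlation of 0.7 without a reason. It also leaves out the within-group tests. Nor is 5% a safe comparator when schools are randomised. The absence of a multiplicity adjustment is therefore not the finding. It would also be wrong to call the analysis wholly unadjusted, since covariance adjustment for confounders is planned, although that does nothing for multiplicity.

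Stage 2 is a further caution. Exploratory factor analysis is meant to discover the questionnaire's dimensions, so neither exactly five domain scores nor a valid total score can be taken for granted.

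What the reply does not answer is that no score and no comparison is named as deciding, while the sample size presupposes one. The stage 2 uncertainty makes it more important to settle this before stage 3 outcomes are examined.

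**Conclusion.** The point holds in a limited form: stage 3 has no named deciding outcome or comparison, and its sample size belongs to one comparison that is not identified. The inflation figures are conditional. They are about 10–23% in either direction, or 5–12% towards benefit against 2.5%, and apply only if five domain scores are each tested at an assumed two-sided 5%, any one suffices, correlations lie between 0.9 and 0, and clustering is ignored. Under an all-domains rule the cost is lost power, not false positives. The weakness of the paired tests as evidence of effectiveness depends on none of these assumptions, because they have no control group.

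**What to change.** In Methods of analysis, state before any stage 3 outcomes are seen that effectiveness is decided by one between-arm comparison. It should compare the total self-care score at post-test, adjusted for the pre-test total, provided stage 2 supports a total score. The analysis should account for school as the unit of randomisation, since a single student-level test would not hold 5%. State that the Delta/S in the sample size formula refers to this score. Treat the domain scores that stage 2 confirms as secondary, and word the expectation in the Results section to match. Report within-group paired changes descriptively only.

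The cost is a few sentences; the pre-test score is already collected and no further data are needed. The downside is that neither a single domain nor a within-group change can then carry the effectiveness claim. With only two schools per arm, an analysis that respects the unit of randomisation will also be less precise than the student-level tests now listed.

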## Discussion

In the first stage, based on the opinions received from the target group, a user-centered educational application for the self-care of adolescents will be designed. In the second stage, after determining the validity and reliability, a questionnaire will be designed to measure the self-care performance of adolescents. In the third stage, using an intervention study for 3 months, the effectiveness of the training will be determined through the designed application.

In the context of the goal of the first stage, our goal in the first stage is to design an application for the self-care of adolescents so that this application is comprehensive and practical and based on the needs and tastes of users. Therefore, it should be noted that designing a mobile phone application by involving users is one of the points that should be considered in the design of health applications. Mobile health projects (mHealth) apply user-centered design (UCD) using patient inputs, careers, physicians, and other stakeholders throughout the project life cycle to create better designs that ultimately could improve efficiency and effectiveness [24–28]. Williams et al. (2014) emphasized that mobile health-tracking applications play a supportive role in self-management rather than replacing current care. Therefore, user-centered mobile health tracking applications may be effective not as stand-alone treatments, but as adjunctive treatments [29]. The study by Young Kim et al. (2020) showed that there were barriers such as security issues, application costs, and the need for user-friendly designs and reliable information for optimal patient use. In addition, healthcare professionals should consider the needs and preferences of patients to promote the acceptance of mobile applications [30]. The goals and results of these two studies are in line with the aim of the 1 stage of our research. In the context of the goal of the second stage, questionnaires are the main means of data collection and there is an increasing need for different questionnaires. Maneesriwongul believes that in the process of questionnaire making, cultural background differences should be taken into account along with the translation of the questionnaire, and the questionnaire should be compatible with the culture of the target community to be valid and reliable. In addition, an assessment questionnaire should be relevant and easily applicable to the target population [31, 32]. In the context of the goal of the second stage, the “Child and Adolescent Self-Care Performance Questionnaire” (CASPQ) examines self-care performance at the ages of 9–18 years in 3 dimensions (global self-care needs, developmental self-care needs, and health deviation self-care needs) using 35 items [33]. Fernández et al. investigated the validity and reliability of this questionnaire in 489 children aged 8–12 years. The results showed that CASPQ shows sufficient metric properties similar to the original questionnaire. For this reason, it is a useful questionnaire for evaluating self-care practices and planning interventions aimed at improving them [34]. The purpose and results of this study are consistent with the purpose of the current study, which is to design a questionnaire to measure self-care performance, but this questionnaire is not comprehensive. Meanwhile, the Congenital Heart Disease Self-Care Questionnaire (CHDSCQ), includes 45 items with 4 subscales (knowledge, adherence, symptom recognition, and health maintenance behaviors), and evaluates self-care status in adolescents and young adults with congenital heart disease. The questionnaire takes approximately 15 min to complete, and higher scores indicate better self-care. In a psychometric study, Pike et al. (2019) examined the self-care questionnaire of adolescents and young adults with congenital heart disease. The results showed that the CHDSCQ is the first valid questionnaire (both content and criteria/clinical validation) to assess self-care in the CHD population [35]. This questionnaire is designed for adolescents with heart disease, which only examines the self-care status related to heart disease in patients and does not have the necessary capacity to evaluate self-care in healthy adolescents. The purpose and results of this study are contrary to the purpose of the current study, which is to design a questionnaire to measure self-care performance in healthy adolescents. In the context of the goal of the third stage, Thornton et al. (2021) conducted a study aimed at multiple health behavior change, a self-monitoring mobile app for adolescents: A development and usability study of the Health4Life app. The Health4Life program is a smartly designed, self-monitoring program for adolescents that simultaneously targets the Big 6 lifestyle behaviors. Adolescents evaluated this program as very acceptable and usable. This program has the potential to effectively modify important risk factors for chronic disease among youth [36]. Also, a study by Alves et al. (2021) was conducted to develop and validate health technology to promote self-care for adolescents with diabetes. The results showed that the use of this program by adolescents, considering that it is a very understandable electronic technology, helps to acquire new knowledge and adhere to healthy practices [37]. The purpose and results of these two studies are consistent with the purpose of the present study, in the field of using a health application to promote health in adolescents.

Also, the study by Antunes et al. (2023) aims to evaluate the impact of an educational intervention associated with physical exercise based on the web in promoting health and quality of life of patients with fibromyalgia in Brazil. which is consistent with the current research in terms of Online educational intervention for self-care and health promotion [38].

From the limitations of this research, it can be said that because little research has been done in the field of application design to improve the health of adolescents, the possibility of comparing the results will be limited. Considering that adolescents are active users of mobile phone applications, it is recommended to design more applications in the field of adolescent health. One of the strengths of this research study is the novelty of the method used to institutionalize self-care and assess adolescents’ health by contemporary technologies, namely mobile applications. Application design with a user-centered approach (in this study, parents, students, and professionals) is another strength of this research. In addition, this research provides a suitable platform for various interventions for adolescents and schools. This method can also be used for other age groups or other diseases and health problems.

This study is an integration of mobile technologies, health education, and health promotion programs in the form of mobile health. Given that the number of mobile phone users is increasing day after day and so is their popularity, it seems that using applications in the field of health seems to be the right decision. The researchers also tried to keep in mind the following considerations such as the application design process, criteria such as user participation, content quality, usability, the need for the program to match the literacy level of users, program security, user privacy, and the possibility of updating the content without the need to update the entire program. The findings of this study can be useful in designing and formulating policies, applications, and programs in the field of health and on how to monitor and guide the health of individuals.

